### 11.4.5 Progression-Free Survival

Defined as the duration of time from registration to progressive disease, local recurrence, distant metastatic disease, or death, whichever occurs first.

### 11.4.6 Overall Survival

Defined as the interval of time from registration until death from any cause.

## 12.0 ETHICAL AND REGULATORY REQUIREMENTS

### 12.1 Protocol Review

The protocol and informed consent form for this study must be reviewed and approved in writing by the UC Davis Scientific Review Committee (SRC) and the Institutional Review Board (IRB) prior to any patient being registered on this study.

### 12.2 Informed Consent

Written informed consent will be obtained from all patients, or the legally authorized representative of the patient, participating in this trial, as stated in the Informed Consent section of the case of Federal Regulations, Title 21, Part 50. If a patient's signature cannot be obtained, the investigator must ensure that the informed consent is signed by the patients legally authorized representative. Documentation of the consent process and a copy of the signed consent shall be maintained in the patient's medical record.

### 12.3 Protocol changes or amendments

Any modification of this protocol must be documented in the form of a protocol revision or amendment signed by the principal investigator and approved by the SRC and the IRB, before the revision or amendment may be implemented. The only circumstance in which the amendment may be initiated without regulatory approval is for a change necessary to eliminate an apparent and immediate hazard to the patient. In that event, the investigator must notify the SRC and the IRB in writing within 10 working days after the implementation.

#### 12.4 Maintenance of Records

If the investigator relocates or for any reason withdraws from the study, then the study records must be transferred to an agreed upon designee, such as another institution, another investigator, or to the UC Davis Clinical Trials Support Unit (CTSUS). Records must be maintained according to sponsor and FDA requirements.

#### 12.5 IRB Reporting of Unanticipated Problems and Adverse Events

Unanticipated Problems (UP) and Adverse Events (AE) will be reported to IRB according to the policies, procedures and guidelines posted on the IRB web site <http://www.research.ucdavis.edu/home.cfm?id=ovc,1,1301>. Fatal and life-threatening UP will be reported to IRB within 7 days of notification of the event. All other UP reports will be submitted to the IRB no later than 15 days after occurrence or notification of the event. Copies of the report documents will be kept in the study regulatory binder.

#### 12.6 MedWatch Reporting

For this investigator-initiated study, the investigator is considered the sponsor. The investigator/sponsor is required to report adverse experiences to the FDA through the MedWatch reporting program, even if the trial involves a commercially available agent. Adverse experiences to be reported include any unexpected (not listed in the package label), serious adverse experiences with a suspected association to the study drug. These adverse experiences will be reported using a MedWatch form 3500 for voluntary reporting. MedWatch forms and instructions are available at [www.fda.gov/medwatch](http://www.fda.gov/medwatch). MedWatch reports can be submitted online at <https://www.accessdata.fda.gov/scripts/medwatch/>

When the serious adverse event is reported to the FDA, copies of the MedWatch 3500 form and supporting materials will be submitted to the UC Davis IRB and the UC Davis CTSU. A copy of the MedWatch 3500 form and supporting materials will be kept on file in the study regulatory binder.

#### 12.7 Inclusion of Women, Minorities and Children

### 12.7.1 Inclusion of Women and Minorities

This study will **not** focus on any particular gender, racial or ethnic subset. **No subject will be excluded from the study on the basis of gender, racial, or ethnic origin.** Male, female and minority volunteers will be recruited for this study from the general population and approximately 50% men and 50% women will be studied. The projected gender, racial, and ethnic composition of the study will represent that of the state of California.

### 12.7.2 Inclusion of Children

In accordance with NIH guidelines on the inclusion of children as participants in research involving human subjects, children under the age of 18 years must be included in all human subjects research, conducted or supported by the NIH, unless there are clear and compelling reasons not to include them. Therefore, proposals for research involving human subjects must include a description of plans for the inclusion of children.

**This protocol does not include children < 18 years of age for the following reason: pediatric soft tissue sarcomas (e.g. embryonal rhabdomyosarcoma, Ewing's sarcoma, etc...) have established and clinically effective chemotherapeutic protocols which have been proven to favorably impact outcome and prognosis in the adjuvant/neoadjuvant setting. Enrolling children < 18 into this investigational protocol would therefore potentially prevent them from receiving established first-line therapy.**

## 13.0 STATISTICAL CONSIDERATIONS

### 13.1 Primary Objective

#### 13.1.1 Phase I Trial

To determine the maximally tolerated dose (MTD) of the antiangiogenic agent sorafenib in combination with preoperative conformal radiotherapy for soft tissue sarcomas of the extremities and the body wall, high grade > 5 cm in diameter and low grade > 8 cm. A traditional dose-escalation design will be used to determine the MTD of sorafenib combined with radiotherapy. 3-6 patients will be evaluated at each of 2 dose levels, based on a starting dose of 200 mg bid derived from preclinical studies of sorafenib combined with radiotherapy. Since 400 mg bid is the well established MTD for sorafenib monotherapy in patients with renal cell carcinoma and hepatocellular carcinoma, the dose will not be escalated above this level even if DLT is not observed.

MTD is defined as the dose that produces dose limiting toxicity (DLT) in 33% of patients. Dose level escalation will be determined based on DLTs observed through the first 70 days of therapy, but DLTs will be monitored in the post-operative period. Dose de-

escalation may occur if excess late DLTs are observed. **See Section 7.1 for further explanation of determination of DLT.** Briefly, if 0/3 patients experience DLT, the dose will be escalated for the next cohort of 3 patients. If 1/3 patient experience DLT, the same dose will be repeated for the next cohort of 3 patients. If 2/3 or 3/3 patients experience DLT, the study will be terminated or dose reduced. Toxicity and wound complication rates will be reported.

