| Anticipated accrual | 
Phase I: Dose-escalation with traditional 3+3 cohort design, 6 to 12 patients.
 
Phase II: 25 patients (anticipated)
                                                                                                                                                                                                                                                                                                                                                                                                                                                                                                                                                                                                                                                                                                                                                                                                                                                                                                                                                                                                                |
| Intervention        | 
Patients will receive neoadjuvant sorafenib (investigational agent) in combination with preoperative external beam conformal radiotherapy (50 Gy in 25 fractions) for localized, large soft tissue sarcomas of the extremity prior to resection with curative intent. Sorafenib is an FDA-approved targeted agent for patients with renal cell carcinoma and hepatocellular carcinoma. Preliminary data suggest activity for sorafenib against soft tissue sarcoma in the metastatic setting. Limited data are available regarding the safety and efficacy of sorafenib in combination with radiotherapy.
 
The Phase I portion of the trial will seek to establish the safety of sorafenib and radiotherapy in the neoadjuvant setting for soft tissue sarcomas of the extremity.
 
The Phase II portion of the trial will aim to determine the pathologic near-complete/complete response rate (<math>\geq 95\%</math> tumor necrosis) of this multimodality therapy. Molecular and dynamic contrast-enhanced MRI studies will seek to establish correlative biological and imaging markers of response and/or resistance to this therapy.
 |

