|  | 
tumor vasculature leads to disordered/poorly regulated tumor perfusion which appears to normalize following delivery of anti-angiogenic agents. This, in turn, allows improved delivery of and susceptibility to cytotoxic agents, which is particularly important with RT since hypoxia is a key mechanism of resistance to this modality. Preliminary clinical data in rectal cancer and malignant brain tumors have demonstrated promising results from the combination of anti-angiogenic agents and RT with respect to downstaging of the primary tumor, local tumor control, and improved progression-free survival. Angiogenic factors are upregulated in patients with STS, and anti-angiogenic agents demonstrate activity against STS in the metastatic setting.
 
Consequently, we propose to evaluate preoperative combined modality sorafenib and conformal RT in patients with STS of the extremity in this prospective trial. Key endpoints will be safety and toxicity in the Phase I trial and pathological response in the Phase II trial. Additional endpoints will include molecular and functional imaging correlative studies of biomarkers of response and resistance to treatment. Enrollment into Phase I will be completed prior to the initiation of phase II.
 
We hypothesize that this combination will be safe and will increase pathologic necrosis within the primary tumor at the time of surgical resection, translating into reduced volume of resected tissue, improved local disease-control, and ultimately improved disease-free survival. Functional imaging studies (dynamic contrast-enhanced MRI) and molecular examination of pre- and post-treatment tumor tissue and serum will allow correlation of changes in tumor blood flow, hypoxia transcription factors, phosphorylated ERK, and angiogenic markers to the degree of tumor necrosis following treatment with preoperative sorafenib and radiotherapy.
 |

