#### 4.0 ACCRUAL GOAL

- Phase I— Dose-escalation schedule comprising 6 to 12 patients (see schema). This sample size is based on a traditional 3+3 cohort design with escalating doses of sorafenib in combination with 50 Gy of conformal radiotherapy delivered in 25 fractions (200 cGy per fraction). Based on preclinical data regarding the radiobiology of sorafenib, sorafenib will be initiated at a dose of 200 mg twice daily, followed by 200 mg Q AM/400 mg Q PM for the 2nd cohort, followed by 400 mg bid for the 3rd cohort. Since 400 mg bid is the well established MTD for sorafenib monotherapy in patients with renal cell carcinoma and hepatocellular carcinoma, the dose will not be escalated above this level even if DLT is not observed. Dose level escalation will be determined based on DLTs observed from initiation of sorafenib/RT until time of surgery.
- Phase II— anticipated number of 25 patients will be enrolled depending on phase I result. Anticipating an improvement in near-complete pathological response ( $\geq 95\%$  tumor necrosis) from 0% with RT alone to 33% with combined sorafenib and RT, we will have an 80% power to detect this difference if we accrue 25 patients, assuming a type I error rate of 5%.

Total target accrual is 30-35 patients depending on results of dose-escalation schedule from Phase I of trial.

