## 7.0 TREATMENT PLAN

### 7.1 Sorafenib Dose Levels and Definition of Dose-Limiting Toxicity

Evaluation for loco-regional toxicity from therapy will occur daily (excluding weekends and holidays) while patient is receiving RT (**see section 10.1 for study calendar**) and then biweekly during the rest period following completion of RT prior to surgical resection. Evaluation for generalized/systemic toxicity (e.g. hypertension, myelosuppression, etc.) will occur weekly (**see section 10.1 for study calendar**) during the treatment phase and then biweekly during the rest phase of the study. Patients will maintain a pill diary so that a record of self-administered medications will be available.

| Dose Level | Sorafenib          | Radiation       |
|-------------------|---------------------------|------------------------|
| 1                 | 200 mg twice daily        | 200 cGy x 25 fractions |
| 2                 | 200 mg q am
400mg q pm | 200cGy x 25 fractions  |
| 2                 | 400 mg twice daily        | 200 cGy x 25 fractions |

A traditional dose-escalation design will be used to determine the MTD of sorafenib combined with radiotherapy. The MTD is defined as the dose that produces dose limiting toxicity (DLT) in 33% of patients. Three patients will be enrolled per dose level, with escalation to the next dose level if no dose-limiting toxicity (DLT) is observed. If one DLT is observed, the dose level will be expanded to a total of 6 patients, and escalation will occur if no more than one DLT is observed among the 6 patients. If 2 or more out of 3 patients, or 3

or more out of 6 patients experience DLT, the study will be terminated or dose reduced to the previous dose level. Dose level escalation will be determined based on DLTs observed from start of treatment until date of surgery, but DLTs will be monitored in the postoperative period, and dose de-escalation may occur if excess late DLTs are observed.

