## 7.2 Sorafenib Dose Modification

7.2.1 General Considerations. According to the following dose level table, sorafenib dosing will be modified for adverse events that are at least in-part *attributable* to sorafenib according to the following sections.

| Dose Level | Sorafenib            |
|------------|----------------------|
| 0*         | 200 mg daily         |
| 1          | 200 mg twice daily   |
| 2          | 200mg am
400mg pm |
| 3          | 400 mg twice daily   |

\*Patients will be removed from protocol treatment if dose reduction below this level is indicated.

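### Section 13.1.1 plans two dose levels while Sections 4.0, 7.1 and 7.2.1 escalate through three, and the accrual figures (6-12 in phase I, 30-35 in total) do not fit the three-level schedule

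*Protocol*

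**What the plan says.** The statistical section and the treatment sections disagree on the number of dose levels.

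- **Protocol, Section 13.1.1:** "3-6 patients will be evaluated at each of 2 dose levels, based on a starting dose of 200 mg bid".
- **Protocol, Section 4.0:** "sorafenib will be initiated at a dose of 200 mg twice daily, followed by 200 mg Q AM/400 mg Q PM for the" second cohort, and then 400 mg twice daily for the third. That is three doses.
- **Protocol, Section 7.1, dose table:** the same three doses in three rows. The third row is numbered 2, as is the second.
- **Protocol, Section 7.2.1, dose table:** the same doses numbered 1, 2 and 3, with "400 mg twice daily" as level 3. Level 0 (200 mg daily) is there only for dose reduction.

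Section 7.1 starts each level with three patients and adds: "If one DLT is observed, the dose level will be expanded to a total of 6 patients".

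The accrual figures are:

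- **Synopsis:** "Dose-escalation with traditional 3+3 cohort design, 6 to 12 patients".
- **Section 4.0, phase I:** "Dose-escalation schedule comprising 6 to 12 patients (see schema").
- **Section 4.0, phase II:** an anticipated 25 patients.
- **Section 4.0, total:** "Total target accrual is 30-35 patients depending on results of dose-escalation schedule from Phase I of trial".

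The synopsis also says "Enrollment into Phase I will be completed prior to the initiation of phase II". No text counts phase I patients toward the 25.

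**The concern.** The number of dose levels is a basic design parameter of a 3+3 trial and determines how many patients phase I can need. Here the section that should fix it gives a number that the dosing sections contradict, and the accrual figures follow that number. Someone reading Section 13.1.1 alone, with its start at 200 mg twice daily and ceiling of 400 mg twice daily, would not expect the intermediate dose.

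The practical consequence is a misstated accrual target. Section 12.3 requires approval of a protocol modification before it is implemented. If the accrual figures had to be raised after a cohort expanded, an amendment could be needed while escalation was under way. The duplicated level number in the Section 7.1 table is a smaller slip, but Section 10.2 sends the reader to Section 7.1 to assign each patient's dose level.

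**Working it through.** **Inputs**

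| Input | Value | Source |
|---|---|---|
| Patients per level, minimum | 3 | Section 7.1 |
| Patients per level, maximum | 6 | Section 7.1, after one DLT |
| Dose levels, statistical section | 2 | Section 13.1.1 |
| Dose levels, dosing sections | 3 | Sections 4.0, 7.1, 7.2.1 |
| Phase II patients | 25 | Sections 4.0, 13.1.2 |
| Printed phase I accrual | 6-12 | Synopsis, Section 4.0 |
| Printed total accrual | 30-35 | Section 4.0 |

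**Step 1: reproduce the printed figures.** With L levels all opened, phase I takes 3L to 6L patients and the trial takes 25 + 3L to 25 + 6L.

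| Levels | Phase I | Total |
|---|---|---|
| 2 | 2×3 = 6 to 2×6 = 12 | 25+6 = 31 to 25+12 = 37 |
| 3 | 3×3 = 9 to 3×6 = 18 | 25+9 = 34 to 25+18 = 43 |
| Printed | 6-12 | 30-35 |

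The printed phase I range is exactly the two-level count. The printed total equals neither row; it is within 2 patients of the two-level row at each end. Working backwards, 30 − 25 = 5 and 35 − 25 = 10, so the total leaves 5-10 for phase I, which differs from the 6-12 in the same section.

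**Step 2: see where the three-level schedule leaves the printed ranges.** With no DLT at any level, phase I takes 9 and the total is 34, inside both ranges. With all three levels opened and one cohort expanded, phase I takes 9 + 3 = 12 and the total is 37, above 35. With two cohorts expanded, phase I takes 15, above 12. At the maximum, the shortfalls are 18 − 12 = 6 in phase I and 43 − 35 = 8 in total. Phase I takes fewer than 9 only if toxicity stops escalation before the third level.

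**Step 3: how often this would happen.** The protocol gives no DLT rates, so the rates below are assumptions chosen to span a range. The 3+3 tree can be enumerated exactly. At a level with DLT probability p:

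- escalate after 3 patients: (1−p)³
- escalate after 6 patients (1/3, then 0/3): 3p(1−p)² × (1−p)³
- stop after 6 patients: 3p(1−p)² × [1 − (1−p)³]
- stop after 3 patients: the remainder

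Section 7.1 escalates at no more than 1 of 6 and stops at 3 of 6, leaving 2 of 6 undefined. Here 2 of 6 is taken to end escalation. No patients are added back at a lower level. N is the phase I size.

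| Assumed DLT rates, levels 1 / 2 / 3 | P(N > 12) | P(N + 25 > 35) |
|---|---|---|
| 2% / 5% / 10% | 0.044 | 0.359 |
| 5% / 5% / 10% | 0.062 | 0.393 |
| 20% / 30% / 40% | 0.092 | 0.308 |
| 5% / 10% / 20% | 0.111 | 0.505 |
| 15% / 25% / 35% | 0.121 | 0.393 |
| 5% / 15% / 30% | 0.130 | 0.512 |
| 10% / 20% / 33% | 0.139 | 0.468 |
| 10% / 15% / 25% | 0.143 | 0.501 |

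The largest P(N = 18) over these profiles is 0.016. If 2 of 6 is instead allowed to escalate, P(N > 12) becomes about 5-26%, so the choice made here is the one that gives the smaller overrun.

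**The case against.** The strongest reply is that the printed figures are expectations and not limits. The synopsis labels its figures as anticipated, and Section 4.0 calls the total a target that depends on the escalation. On that reading, setting 12 against 18 compares a planning range with a worst case reached in at most 1.6% of the runs above. Phase I stays at 12 or fewer in 86-96% of them, and a trial with few DLTs finishes inside both ranges. This much stands: nothing in the protocol makes 12 or 35 a hard cap, and the need for an amendment is an inference from Section 12.3, not a stated consequence. It does not rescue the figures, because 6-12 is a count for a different number of levels, and a single expansion with all three levels opened already exceeds 35.

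A second reply is that phase I patients treated at the maximum tolerated dose might count toward the 25, which would lower the total. No text says so. The synopsis completes phase I enrolment before phase II starts, and the power statement in Section 13.1.2 rests on accruing 25. If the sponsor does intend this, it should be written down, and the 34-43 would then be too high.

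A third reply is that the total of 30-35 is simply rounded, since even two levels give 31-37. That may be so. It is then a separate looseness and not further proof of the dose-level conflict.

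Finally, the three places that list the doses agree with one another, so treating staff are unlikely to give a wrong dose. The table numbering in Section 7.1 is only a labelling slip, settled by Section 7.2.1. The schema in Section 5.0 is a figure not available for this review and could not be compared.

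**Conclusion.** The point holds. Section 13.1.1 gives the wrong number of dose levels for the schedule in Sections 4.0, 7.1 and 7.2.1, and the phase I accrual of 6-12 follows the wrong number. With all three levels opened, the protocol's own rule takes 9-18 patients in phase I and 34-43 in total.

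The counts need only the 3-to-6 rule, three levels, and 25 phase II patients counted separately. The probabilities (4-14% for phase I above 12, 31-51% for the total above 35) rest on assumed DLT rates and on how the undefined 2-of-6 outcome is handled. They are indicative only, and the finding does not depend on them.

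This should be fixed because a number of dose levels and a sample size are wrong as written. It does not touch the phase II endpoint, its power or its type I error.

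**What to change.** Make these text corrections in four places:

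1. **Section 13.1.1:** change the number of dose levels from 2 to 3.
2. **Section 7.1, dose table:** number the third row (400 mg twice daily) as level 3, as Section 7.2.1 does.
3. **Section 4.0:** restate phase I as up to 18 patients (9-18 if all three levels open) and the total as up to 43 (34-43 if all three open).
4. **Synopsis:** restate the phase I figure in the same way.

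The dose sequence and the escalation rule stay as they are. Actual enrolment exceeds the printed upper limits only if cohorts expand, by at most 6 patients in phase I and 8 in total.

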#### 7.4 Radiation

Initiation of conformal radiotherapy will be considered day 1 of study treatment. Treatment will consist of a total dose of 50 Gy (delivered in 25 fractions of 200 cGy over approximately 35 days). If treatment falls on a weekend or holiday, treatment can resume the next business day. The target volume of radiation therapy will include the site of the primary lesion and those tissues suspected of involvement by microscopic disease to a clinically important probability. Physical exam in conjunction with MRI and/or CT scans obtained during evaluation will be used to define the target volume. Treatment planning will aim to include a radial margin of approximately 2 cm and a longitudinal margin of approximately 3 cm beyond the gross disease.

Optimal field arrangement, beam parameters, and shaped blocks will be used to achieve the closest approximation of treatment volume to target volume to minimize irradiation of uninvolved normal tissue. Immobilization devices will be used daily to ensure reproducibility of treatment protocols. All possible efforts will be made to avoid treating the full circumference of an extremity or treating the lung. Patients may receive post-operative brachytherapy or external beam radiation therapy for positive microscopic surgical margins. Boost will not be given for patients with 100% necrosis. If indicated, RT may begin approximately 2 weeks following surgical resection, assuming there is satisfactory healing of the surgical wound. The target volume for the post-operative RT will be the tumor bed as defined by the operative and pathological findings.

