#### 7.5 Surgery

Surgical resection will take place on approximately day 50 – 90 of the study, occurring approximately 3 to 7 weeks following completion of combined neoadjuvant sorafenib/RT (**see study calendar, section 10.1**).

Surgical treatment necessary to resect the tumor with negative margins will be used. Biopsy sites will be excised en bloc with the definitive surgical specimen. The goal of surgical resection is to remove a 2 cm margin of normal tissue around the tumor without compromising function. Surgical dissection will take place through normal tissue planes and, where technically possible, will be done through a fascial plane outside the tumor. If the tumor is close to or displaces major vessels or nerves, these structures will be preserved if the adjacent adventitia or perineurium can be removed and the margin is not involved pathologically. If postoperative pathologic evaluation reveals positive soft-tissue margins other than bone, nerve, or large blood vessels, this margin should be re-resected if possible. If bone, major blood vessel, or nerve is microscopically positive, additional radiation may be given as noted above. In general, lymph node dissection will not be performed, but a sampling can be performed if the primary tumor is over a major node station. Closed wound suction drainage should be used in all anatomic regions to evacuate postoperative seroma fluid. The drains should exit the skin close to the edge of the surgical incision. External

compression for extremity resections with ace wraps or compression dressings is also advised. Because all patients will have had radiation, special care must be given to skin flaps. Use of muscle flaps, pedicled myocutaneous flaps, and even free flaps is encouraged to fill dead space, particularly if there is any concern about the viability of the wound flaps. In general, the following principles should be followed in post-operative management of these patients:

- Maintain staples or skin sutures per surgeon preference but because of potential delay in wound healing, 3-4 weeks is recommended
- Leave drains until the drainage meets the criteria for surgeon preference for discontinuation
- Begin rehabilitation slowly

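### Section 13.1.1 ends the dose-escalation DLT window at day 70, while Sections 4.0 and 7.1 end it at surgery, which may fall on about day 50 to 90

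*Protocol*

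**What the plan says.** Three sections of the protocol state which DLTs decide dose escalation.

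- Section 4.0: "Dose level escalation will be determined based on DLTs observed from initiation of sorafenib/RT until time of surgery".
- Section 7.1: "Dose level escalation will be determined based on DLTs observed from start of treatment until date of surgery".
- Section 13.1.1: "Dose level escalation will be determined based on DLTs observed through the first 70 days of therapy".

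Sections 7.1 and 13.1.1 both add a provision for later events. Section 7.1 says that "DLTs will be monitored in the postoperative period, and dose de-escalation may occur if excess late DLTs are observed". Section 13.1.1 continues, "but DLTs will be monitored in the post-operative period", allows de-escalation for an excess of late DLTs, and then refers the reader back: "See Section 7.1 for further explanation of determination of DLT".

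On timing, radiotherapy is "delivered in 25 fractions of 200 cGy over approximately 35 days" (Section 7.4), and its first day is study day 1. Surgery is placed on about day 50 to 90, "occurring approximately 3 to 7 weeks following completion of combined neoadjuvant sorafenib/RT" (Section 7.5). Calendar 10.1 heads the surgery column weeks 8 to 12 and prints day 70 beneath.

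On safety bloods, Section 7.1 requires systemic toxicity, with myelosuppression as a named example, to be evaluated weekly during treatment and biweekly in the rest phase, and cites Calendar 10.1. The calendar ticks a doctor's visit with blood pressure in each of the five treatment weeks, but blood tests only in week 2. Schedule of Events 10.4.4 lists the CBC before registration and at pre-surgical restaging, then as needed. It has no on-treatment column.

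**The concern.** The three sentences state one decision rule with two different end points. The end points coincide only if surgery falls on day 70, and nothing in the protocol fixes it there. For a patient operated on later, a DLT after day 70 but before surgery enters the 3+3 count under Sections 4.0 and 7.1 and not under Section 13.1.1.

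The cohorts are small enough for this to matter. One additional DLT turns 0 of 3 into 1 of 3, so the dose is repeated instead of escalated. It turns 1 of 3 into 2 of 3, so the study is terminated or the dose reduced instead of the cohort being expanded. The MTD is the Phase I primary objective, and the Phase II dose is taken from it.

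The secondary concern is detection. The DLT definition in Section 7.1 includes grade 4 neutropenia for more than 7 days and grade 4 thrombocytopenia for more than 5 days. These can be seen only in blood counts, and the visit tables do not schedule counts at the frequency that Section 7.1 requires.

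**Working it through.** **Inputs.** Radiotherapy takes about 35 days (7.4). Surgery follows 3 to 7 weeks later, printed as about day 50 to 90 (7.5). The surgery column is weeks 8 to 12, with nominal day 70 (10.1). The escalation cut-off is day 70 (13.1.1) or surgery (4.0 and 7.1). The 70 days are assumed to run from study day 1.

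**Range of surgery days.**
- From the interval: 35 + 21 = day 56 and 35 + 49 = day 84.
- From the calendar weeks: week 8 starts on day 7 × 7 + 1 = 50, and week 12 ends on day 12 × 7 = 84.
- Printed in 7.5: day 50 to 90.

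Day 70 is therefore one day within a wide range and does not mark the end of the pre-operative period. Week 11 (days 71 to 77) and week 12 (days 78 to 84), 2 of the 5 weeks in the surgery column, lie wholly after it.

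**Difference between the two windows (surgery day minus 70).**

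| Surgery day | Difference | Effect of the day-70 rule, read literally |
|---|---|---|
| 50 | −20 | 20 post-operative days counted |
| 56 | −14 | 14 post-operative days counted |
| 70 | 0 | windows agree |
| 84 | +14 | 14 pre-operative days not counted |
| 90 | +20 | 20 pre-operative days not counted |

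The last two rows carry the point. The first two are weaker, because Section 13.1.1 itself sets its window against the post-operative period and so probably does not mean to include events after surgery.

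**An example.** Take a patient operated on at day 84 who has a DLT on day 75. Under Sections 4.0 and 7.1 the event counts towards escalation. Under Section 13.1.1 it is too late for the escalation window, yet it precedes the post-operative period.

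**Safety bloods.** In weeks 1 to 5 the calendar ticks a doctor's visit 5 times and blood tests once. Week 2 ends on day 14, and the first rest-phase draw is in week 6, which starts on day 5 × 7 + 1 = 36. Days 15 to 35, that is 35 − 14 = 21 days at the least, have no scheduled draw. The DLT durations to be detected are more than 7 and more than 5 days.

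**The case against.** The strongest reply is that day 70 is not a rival design. It is the nominal surgery day in the calendar. Section 13.1.1 contrasts its window with the post-operative period, points to Section 7.1 and goes on to present its 3+3 rules as a summary. Two concordant sections say surgery, so a careful reader would probably apply that. This explains where the figure comes from, but it does not settle the rule. The pointer is to how a DLT is determined, and nothing says that the 7.1 window overrides the 70 days just stated.

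A second reply is that excess late DLTs may trigger de-escalation in any case, and in Section 13.1.1 that sentence is not confined to events after surgery. A day-75 event could therefore still affect the dose. That is fair, but the provision is discretionary and does not define the 3+3 count.

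A third reply concerns the remedy. Day 70 is the only fixed limit in the three sections, and removing it leaves the window open for a patient who never has surgery. Section 7.5 takes patients with unresectable tumors off protocol, and Section 7.7 lists other reasons for stopping. This stands, so the new wording needs a maximum day.

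On the bloods, the calendar row may show the correlative draws: Section 10.5 reads the calendar as weeks 2, 6, 9 and end of study. Section 7.1 already requires the weekly evaluation, so the tables can be seen as merely incomplete. That keeps the point secondary. The mismatch remains, because neither table schedules a weekly count.

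A reader might infer that laboratory DLTs would go unseen. The documents do not show this: unscheduled counts are not barred, and the duration rules in Section 7.2.4 imply repeat counts once a grade 4 value is known. The gap is in scheduling first detection.

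**Conclusion.** The inconsistency is real and should be corrected. Section 13.1.1 conflicts with Sections 4.0 and 7.1 on which events decide escalation. The exposure is up to 14 pre-operative days if surgery follows 3 to 7 weeks after a 35-day course, and up to 20 at the printed limit of day 90. It arises only for patients operated on after day 70 who have a qualifying event between day 70 and surgery.

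A reader might infer that the trial would probably select the wrong MTD. The documents do not support that. They give no DLT rate by time, so no probability of a wrong decision can be derived. Nor should the point be read as an established counting of wound complications after early surgery, since Section 13.1.1 separates out the post-operative period.

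The blood-count point is secondary: one scheduled draw in five treatment weeks, possibly a correlative one, against a weekly requirement.

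**What to change.** **Escalation window.** In Section 13.1.1, replace the 70-day clause with a window that runs from start of treatment until the date of surgery, or until day 90 for patients who do not have surgery. Use identical wording in Sections 4.0 and 7.1. State that post-operative events are handled by the existing late-DLT monitoring and de-escalation provision and do not enter the 3+3 count. The cost is one clause in each of three sections and one added sentence. A cohort decision may wait until the last patient's surgery, up to 14 days past day 70 and 20 at day 90; Sections 4.0 and 7.1 already require this wait.

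**Safety bloods.** Add CBC and chemistry weekly in weeks 1 to 5, and biweekly in the rest phase, to both Calendar 10.1 and Schedule of Events 10.4.4. The latter needs an on-treatment column. Changing the calendar alone would leave the table that actually names the CBC out of step. Label the safety draws separately from the correlative draws of Section 10.5. The cost is about four extra on-treatment draws per patient (weeks 1, 3, 4 and 5), which can be taken at visits already scheduled.
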